## 1.3 Frequency and duration of follow-up

Data on all the outcome measures was collected at baseline and end-line assessment.

The participants were recruited in June 2015.

## 1.4 Data collection

The data were collected at two points; baseline and end-line assessment at 8 month from baseline.

The baseline assessment was completed in July 2015 and the end-line assessment in March/April 2016.

Inclusion criteria

- All the students enrolled and studying in class IX
- Present in the school on the day of assessment

Exclusion criteria

- None

Following data is collected from consented participants: (through contact information form)

Complete name (will not be part of the questionnaire and linked directly with the outcome assessment questionnaire)

Complete address and contact details, if available (will not be reported)

- Class, section, and roll number
- Age (in years)
- Gender
- Caste
- Marital status
- Father’s education
- Mother’s education
- Father’s occupation
- Mother’s occupation
- Baseline measures of the primary, secondary and exploratory outcomes (listed below)

Outcome Measures

The primary outcome measure is overall school climate. The secondary outcome measures are attitudes towards gender equity, knowledge of and attitude towards reproductive and sexual health, experience of bullying, violence, and depression. In addition, the following exploratory^^[[1]](#footnote-2)^^ outcome measures will also be assessed: tobacco, alcohol and other substance use, sexual behaviour, and suicide attempts. The outcome assessment measures are summarised in Table 1.

Table 1: SEHER Trial outcome assessment measures

| Outcome Indicator | Instrument | Description |
| --- | --- | --- |
| Primary Outcome | | |
| School climate | Beyond Blue School Climate Questionnaire (BBSCQ) | 28 items questionnaire; minimum and maximum score range between 0 and 28 with higher scores indicating a more favourable experience of School Climate |
| Secondary Outcome | | |
| Experience of bullying | Illinois Bullying Scale | 4 items questionnaire; score ranges between 0 and 12 with higher scores indicate experience of severe bullying; recall period: last 30 days |
| Violence (perpetration and victimisation) | Global School-based student Health Survey (GSHS) | 4 items; 2 items each on perpetration and experience of physical violence; recall period: last 8 months (since the class IX started) |
| Attitude towards gender equity | Gender Equitable Men Survey | 10 items questionnaire; minimum and maximum score range between 0 and 10 with higher scores indicating more positive attitude towards gender equity |
| Knowledge of and attitude towards RSH | Questionnaire on knowledge and attitude of towards RSH | 8 items questionnaire; minimum and maximum score range between 0 and 8 with higher scores indicating better knowledge of and attitude towards RSH |
| Depression | Patient Health Questionnaire-9 | 9 items; minimum and maximum scores range between 0 and 27 with higher scores indicating severe depression; recall period: last 2 weeks |
| Exploratory Outcome | | |
| Substance use | GSHS | 14, items measure use of tobacco (chewing and smoking), alcohol and other substances in last 8 months (since the class IX started) and last 30 days, frequency of use in last 30 days |
| Sexual behaviour | GSHS | 4 items measure sexual behaviour, and experience of forced sex in last 8 months (since the class IX started) |
| Suicide attempts | GSHS | One item measures suicide attempt in last 8 months (since the class IX started) |

Process indicators

The coverage of each component, the quality of intervention implementation (fidelity), and the extent to which stakeholders engaged with it will be examined. Coverage indicators are collected through monthly reporting forms and quality indicators are assessed through ratings of specific components, such as the wall magazine and peer group meetings by respective supervisors, and the observations made by the intervention team during field visits. The stakeholder engagement will be examined through students’ reporting of self-coverage of intervention at the follow-up assessment.

Whole school level activities

- Number of awareness meetings held with students against planned per month
- Number of awareness meetings held with teachers against planned per month
- Number of wall magazines produced against planned per month
- Types of topics covered through wall magazine
- Number of questions addressed against questions received per month through speak-out box
- Types of questions received through speak-out box per month
- Reasons for not addressing certain issues
- Type of competitions organised against planned per month
- Number of students participated in each competition
- Number of School Health Promotion Committee meetings held against planned
- Number of health policies generated and implemented in the school

Group school level activities

- Number of peer groups formed per school
- Number of peer group meetings conducted against planned per month
- Number and types of issues addressed in peer group meetings
- Number of workshops organised for students against planned
- Students’ feedback on the workshop organised for them
- Number of workshops organised for teachers against planned
- Teachers’ feedback on the workshop organised for them

Individual level activities

- Number of students availed counselling services (total, and gender wise)
- Number and types of referrals
- Types of issues addressed
- Number of cases referred for specialist treatment

Fidelity of the intervention

- Description of the SEHER *Mitra* and Teacher as SEHER *Mitra* (mean age, and average years of education and experience)
- Total number of supervisory visits
- Fortnightly reports by the supervisors
- Monthly wall magazine rating by the supervisors
- Monthly peer-group meeting rating by the supervisors

At the follow-up assessment, the self-coverage data of the SEHER intervention and AEP activities is collected from the students.

SEHER intervention self-coverage

- Awareness about the SEHER intervention
- Participation in the assembly
- Contribution to wall magazine
- Number of wall-magazines read
- Awareness about the speak out box
- Participation in the competition/s
- Knowledge of health policies
- Availed counselling services

Tarang-AEP self-coverage

- Aware about the Tarang-AEP
- Name of the Tarang-AEP teacher
- Number of class-room sessions attended
- Topics of the session attended

## 1.5 Brief description of proposed analyses

Analyses will be carried out by the Trial Manager ([name]) in collaboration with [name] at LSHTM. Analyses will follow CONSORT guidelines for cluster-randomised trials. The primary analysis data will be analysed under intention-to-treat assumptions (i.e. analyse all those with data from three arms irrespective of intervention received).

Analyses will be conducted in Stata version 14. Do-files will be prepared based on blinded data, and data will not be unblinded until the dataset is finalized, locked and sent to the DSMB chair.

# 2 Data analysis plan –Data Description

## 2.1 Recruitment and representativeness of recruited participants

A CONSORT flow chart will be constructed –see Figure 1. [2] This will include the number of eligible schools for random allocation, random allocation of clusters to either intervention arms or comparison arm, arm-wise total number of class IX student enrolment, number of participants recruited in each arm, number of participants refusing, the number of participants covered at the follow-up assessment, number of participants lost to follow-up and the numbers analysed.

Figure 1: SEHER trial flow chart

Total number of secondary schools in Nalanda district (n=136)

Did not meet eligibility criteria (n=24)

Eligible schools for random allocation (n=112)

Randomly selected 75 schools for random allocation to trial arm

**SM arm**

25 schools;

AEP plus SEHER

**Comparison arm**

25 Schools;

Only AEP

**TSM arm**

25 schools;

AEP plus SEHER

One TSM school did not receive the intervention because the school administration was not comfortable with the intervention content

**Received intervention**

25 clusters

Average cluster size (class IX students) (n=304)

**Received intervention**

24 clusters^*^

Average cluster size (class IX students) (n=269)

**Received intervention**

25 clusters

Average cluster size (class IX students) (n=300)

**Baseline Survey**

Total class IX student

enrolment (n=6447)

Parental refusal (n=16)

Participant refusal (n=0)

Assessment completed (n=4046 (62.7%))

**Baseline Survey**

Total class IX student

enrolment (n=7502)

Parental refusal (n=43)

Participant refusal (n=10)

Assessment completed (n=4525 (60.3%))

**Baseline Survey**

Total class IX students

enrolment (n=7601)

Parental refusal(n=10)

Participant refusal (n=07)

Assessment completed (n=4465 (58.7%))

**Endpoint Survey**

Clusters (n=25)

Participant refusal (n=10)

Assessment completed (n=4623 (60.8%))

**Endpoint Survey**

Clusters (n=25)

Participant refusal (n=07)

Assessment completed (n=5316 (70.8%))

**Endpoint Survey**

Clusters (n=24)

Participant refusal (n=06)

Assessment completed (n=4475 (69.4%))

**Analysed**

Clusters (n=25)

Participants (n=4623)

**Analysed**

Clusters (n=25)

Participants (n=5316)

**Analysed**

Clusters (n=24)

Participants (n=4475)

## 2.2 Baseline comparability of arms

Characteristics of participants at baseline will be compared by arm, summarised using mean and standard deviation, median and inter-quartile range, or numbers and proportions as appropriate. No significance testing will be done as differences will be due to chance if the randomisation was correctly applied.

The baseline variables that will be summarised for participants are as follows:

- Age
- Gender
- Caste
- Marital status
- Father’s education
- Mother’s education
- Father’s occupation
- Mother’s occupation
- Overall school climate
- Total score on PHQ-9 (depression)
- Total score on Gender Equitable Men Survey
- Total score on RSH questionnaire
- Experience of bullying
- Experience of violence

For outcome indicators like school climate, depression, attitude towards gender equity and knowledge of reproductive and sexual health, we will transform the data e.g. histograms within each arm will be plotted in order to assess how closely the scales follow a normal distribution to determine how to describe the outcome. Transformations will be carried out if the continuous data are not normally distributed.

Continuous data that are approximately normally distributed will be summarised in terms of the mean, standard deviation, median, minimum, maximum and number of observations. Skewed data will be transformed as appropriate to be normally distributed, or if a transformation is not possible, will presented in terms of the maximum, upper quartile, median, lower quartile, minimum and number of observations. Categorical data will be summarised in terms of frequency counts and percentages.

The following school-level variables will be summarised by arm using numbers (SD) and proportions.

- Type of school
- Nature of school
- Total number of students
- Total number of teachers
- School infrastructure, assessed by number of classrooms, toilets, drinking water facility, etc.

## 2.3 Loss to follow-up

The numbers and proportion of participants lost at end-line will be reported by arm. The data for those lost at end-line will be shown in the CONSORT flow chart.

## 2.4 Descriptive statistics for outcome measures

The primary outcome measure will be summarised by arm at end-line.

The data will be studied to identify outliers and check for data errors.

A similar approach will be followed for the secondary outcomes (listed in section 1.4).

## 2.5 Description of intervention processes

The SEHER *Mitra*, Teacher as SEHER *Mitra* and supervisors will be described in terms of age, experience and education.

The intervention coverage will be reported with proportions and means, as appropriate, and compared between intervention arms (the coverage indicators are listed in the section 1.4).

For all three arms, the Tarang-AEP coverage will be reported and compared with mean, proportion/rates, as appropriate (the coverage indicators are listed in the section 1.4).

# 3 Data analysis plan –Inferential analysis

## 3.1 Main analysis of intervention differences

The main statistical analyses will estimate the standardised mean difference (effect size i.e. mean difference/SD) for school climate by arm at the 8 months follow-up assessment, adjusting for baseline school climate at the school level.

### *3.1.1 Analysis of primary outcome*

The estimation of the SMD of the total score on the BBSCQ at 8 months between i) the TSM and comparison arm; ii) SM and comparison arm, and iii) the SM and TSM arm will address research objective #1, 2, and 3 respectively, see Section 1.1:

Data will be analysed at individual-level using an intention-to-treat (ITT) analysis, using a linear mixed effects model with outcome of the BBSCQ total score at 8 months with intervention arm as a covariate, and adjusting for the school-level BBSCQ score at baseline. A random effect will be included to account for clustering at school level [2-3].

Sensitivity analyses for participants who have completed both baseline and follow-up assessment (cohort analyses): Independent ANCOVA-type analysis for sample of students who have completed both base and end-line assessment, using a linear mixed effects model with outcome of BBSCQ total score at 8 months with intervention arm as a covariate and adjusting for the BBSCQ total score at baseline and school. A random effect will be included to account for clustering at school level.

The data of the students who have completed base and end-line assessment will be matched through the unique identity number given to each participant.

For gender segregated sample for the participants who have completed end-line assessment: Independent ANCOVA-type analysis for sample of only boys and girls, using a linear mixed effects model with outcome of BBSCQ total score at 8 months with intervention arm as a covariate and adjusting for the school-level BBSCQ score at baseline. A random effect will be included to account for clustering at school level.

Model assumptions of normally distributed data, and the missing at random assumption, will be tested (see section 3.1.3) and if necessary, the outcome analyses will be adapted as appropriate.

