## 1.2 Trial design including blinding

SEHER is a cluster-randomised controlled trial (CRT) comparing clusters (schools) in: (i) Teacher-as SEHER *Mitra* (TSM) and ii) SEHER *Mitra* (SM) arms versus the control arm (Tarang-Adolescence Education Programme) with follow up over 8 months.

The trial is conducted in 74 schools (24 in TSM arm, 25 in SM arm and 25 in comparison arm) across 20 blocks of Nalanda district of Bihar. All the students studying in class IX in the academic year 2015-16 are invited to participate in the study at each school. In the SEHER *Mitra* arm the SEHER intervention is delivered by a trained lay worker called as SEHER *Mitra*; in the teacher-as SEHER *Mitra* arm, the SEHER intervention is delivered by a trained teacher called a Teacher-as SEHER *Mitra*.

The Tarang- Adolescence Education programme is delivered in all three arms by the nodal teachers selected and trained by the Department of Education with technical assistance from Centre for Catalysing Change, India.

The random allocation of the schools has been carried out by an independent statistician who is not involved in the Trial.

Outcome measures are administered by researchers independent of the intervention and blind to the allocation of the intervention.

The data analyst will be blinded to the clusters’ allocation.

- 1. **Method of allocation of schools**

Of the 136 total of secondary and higher secondary schools in Nalanda, 112 schools that were eligible for inclusion in the trial were identified based on the following criteria:

- Current implementation of Tarang- AEP
- Total number of students in grade IX in a school >100
- Total number of employed teachers in a school >/=4

Of the 112 schools, 75 were randomly selected for the random allocation. To have a representative pool of 75 schools, and to ensure an equal number of schools of each type in each of the three trial arms, we selected 68% of co-educational (63 out of 93), 69% of only girls’ (9 out of 13) and 50% only boys’ schools (3 out of 6). All the 75 schools are allocated to comparison or one of the intervention arms by using minimisation. To carry out the allocation by minimisation [1], the arms were balanced on the following variables (classifying each of the variables into categories):

1. Type of school (secondary=1; and secondary and higher secondary school=2);
2. School size (small=101-300 students in school; medium=301-600, and large=601 and above students ), and

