3. Nature of school (Co-education=1; only boys’=2; and only girls’=3).

The random allocation by using minimization was carried out by an independent statistician ([name], LSHTM) using the R software package.

- 1. **Sample size estimation**

The sample size estimations are based on for the changes in the primary and a secondary outcome measure, *viz.* school climate and being bullied, for the total as well gender segregated sample. The average score for school climate and the prevalence of being bullied is drawn from the data collected during the pilot testing of the SEHER outcome assessment questionnaire. The assumptions are:

- The arithmetic mean score on Beyond Blue School Climate scale is 20.6 (SD 6.7) with an ICC of 0.018.
- 18% students in secondary school in Nalanda, Bihar reported experiencing bullying in the last 30 days (were made fun of with sexual jokes, comments, or gestures) with an ICC of 0.03.
- The cluster number is 24 in TSM, 25 each in SM and comparison arm and average cluster size is 115 (60 boys and 55 girls).
- Assumed 15% loss to follow-up.

Based on these assumptions, the proposed trial will have 98% power to detect an effect size of 0.2 (difference in means/SD) school climate score between the comparison and each intervention arm respectively, with 95% confidence and an ICC of 0.02 (88% and 93% power among boys & girls, respectively). The trial will have 83% power to detect a 6% absolute difference in the proportion of students who reported experiencing bullying between the comparison and each intervention arm respectively, with 95% confidence and an ICC of 0.03 (82% and 83% power to detect a 7% and 6% difference among boys and girls, respectively).

- 1. **Duration of the intervention period**

In each intervention arm school (SM and TSM), the SEHER intervention activities were conducted between July 2015 and February 2016. The SEHER intervention activities were delivered at three levels viz. whole-school, group and individual level.

Whole school level activities: Awareness generation, wall-magazine, speak-out box, intra school competitions, healthy school policies, and School Health Promotion Committee.

Group level activities: Peer groups of class IX students, and workshops for class IX students and for all teachers.

Individual level activities: Counselling and referral services for all the students in the school.

These activities were conducted all through the 8 months.

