### *3.1.3 Statistical considerations*

*Time points*

The primary analysis will be of the 8 months outcome for total score on the BBSCQ.

*Clustering*

School (cluster) will be included as a random-effect covariate in the regression.

*Covariates*

Socio-demographic variables such as age, marital status, caste, and parents’ education and occupation will be included as covariates in the analysis model, irrespective of arm-wise balances among them at baseline.

*Adjustment for multiple outcomes and reporting p-values*

Interpretation of the intervention effect will be based on the strength of evidence of effect size and consistency of results for related outcomes.

*Missing outcome data*

Missing outcome data will be imputed using multiple imputations, implemented in Stata.

*Model assumption checks*

The models assume normally distributed outcomes; this will be checked when describing the data. Model residuals will also be plotted to check for normality and inspected for outliers. If substantial departures from normality occur, transformations will be considered. If a suitable transformation cannot be found, a non-parametric analysis will be considered.

A sensitivity analysis that assesses the effect of deviations from the missing at random assumption on the intention to treat treatment differences for the primary outcome may be considered if there are considerable amounts of missing data (6). Sensitivity analysis will be conducted comparing results with and without imputation.

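### The models leave out the three factors on which schools were minimised, and the primary covariate list is left open

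*SAP*

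**What the plan says.** On allocation, SAP section 1.2 states "All the 75 schools are allocated to comparison or one of the intervention arms by using minimisation", and that "the arms were balanced on the following variables (classifying each of the variables into categories". The three variables are:

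- "Type of school (secondary=1; and secondary and higher secondary school=2" (two levels)
- "School size (small=101-300 students in school; medium=301-600, and large=601 and above students" (three levels)
- "Nature of school (Co-education=1; only boys’=2; and only girls’=3" (three levels)

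On analysis, section 3.1 describes the main estimate as "adjusting for baseline school climate at the school level". Section 3.1.1 specifies a linear mixed model "with intervention arm as a covariate, and adjusting for the school-level BBSCQ score at baseline", with a random effect for school. The gender-stratified models follow the same form, and 3.1.2 says the secondary outcomes are handled similarly.

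Under Covariates, section 3.1.3 names age, marital status, caste and parents' education and occupation by way of example, and says these "will be included as covariates in the analysis model, irrespective of arm-wise balances among them at baseline". Sections 3.1 and 3.1.1 do not mention them. No section places type, size or nature of school in any model.

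**The concern.** Minimisation makes the arms alike on the chosen factors. Any between-school variation due to those factors is therefore largely removed from the comparison of arms. A model that omits them leaves that variation in the estimated school variance, and so in the standard error. The school random intercept does not correct this, because it is where the unexplained variation is collected. If the factors are prognostic, the reported interval is wider than the design warrants and the true type I error falls below 5%. The precision that the allocation bought is not used.

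The second issue is one of specification. Section 3.1.3 brings in a set of covariates that the primary model statement does not contain, and the set is given by example. Two analysts following the SAP could fit different covariates and report different primary estimates.

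**Working it through.** **Inputs from the SAP (1.2 and the flow chart in 2.1).** There are 24, 25 and 25 schools, with 115 students per school and 15% loss, so m = 115 × 0.85 = 97.75. The ICC is 0.02, the target effect is 0.2 SD, and alpha is two-sided 0.05 (read from the 95% confidence stated). Achieved end-line numbers per school are 4623/25 = 184.9, 5316/25 = 212.6 and 4475/24 = 186.5.

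**The plan's own power figure.** Design effect = 1 + (97.75 − 1) × 0.02 = 2.935. Effective numbers are 24 × 97.75/2.935 = 799 and 25 × 97.75/2.935 = 833. SE = √(1/799 + 1/833) = 0.0495 SD. Then 0.2/0.0495 − 1.96 ≈ 2.08, which gives 98.1% power (98.3% for 25 against 25 schools). The stated 98% reproduces.

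**Effect of omitting the factors.** Let vb be the between-school variance left after the baseline score (total variance set to 1), w = 0.98/m, and R² the share of vb that the three factors explain. The ratio of interval widths, omitted to included, is

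√[(vb + w) / (vb(1 − R²) + w)].

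The SAP gives neither R² nor the share explained by baseline, so both are assumed over a range. If baseline explains nothing, vb = 0.02; if it explains half, vb = 0.01. Example at m = 97.75, w = 0.01003, R² = 0.25 and vb = 0.02: √(0.03003/0.02503) = 1.095.

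| R² | Planned m, baseline explains nothing | Planned m, baseline explains half | Achieved m, baseline explains nothing |
|---|---|---|---|
| 0 | 0% | 0% | 0% |
| 0.10 | 3.5% | 2.6% | 4.2–4.3% |
| 0.25 | 9.5% | 6.9% | 11.6–12.0% |
| 0.50 | 22.4% | 15.4% | 28.6–29.8% |

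**Simulation check.** 75 schools (63 co-educational, 3 boys', 9 girls') were minimised on the three factors and analysed on school means, with 2,500 runs per setting, m = 97.75 and no baseline score. The split of schools by type and size was assumed. Two settings of the minimisation's randomness gave nearly the same answers; both are shown.

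| R² | Width ratio, omitted/included | Type I error, omitted | Type I error, included |
|---|---|---|---|
| 0 | 0.993, 0.990 | 0.054, 0.049 | 0.056, 0.047 |
| 0.10 | 1.030, 1.025 | 0.050, 0.046 | 0.056, 0.048 |
| 0.25 | 1.090, 1.086 | 0.031, 0.034 | 0.049, 0.052 |
| 0.50 | 1.224, 1.220 | 0.019, 0.023 | 0.051, 0.053 |

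The simulation error on a 5% rate is √(0.05 × 0.95/2500) = 0.004. At R² = 0, including the factors widens the interval by about 1%. Power at 0.2 SD was about 98% or more in every setting, with or without the factors.

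**Degrees of freedom.** (2 − 1) + (3 − 1) + (3 − 1) = 5, out of 74 schools.

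**The case against.** The case for leaving the model alone has several parts.

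- **The loss is conditional.** A reader might infer that the intervals are too wide as a matter of fact. The SAP does not support that. It gives no association between the factors and school climate, and the school-level baseline score may already absorb much of it. This stands, and it is why the size is given as a range starting at zero.
- **The error is on the safe side, and the trial is well powered.** A reader might infer a material loss of power. At the effect the SAP plans for, power is about 98% or more under either model. A visible gap appears only for smaller effects that the SAP does not target. This also stands. What remains is an interval that may be wider than it need be.
- **The analyst is blinded.** A reader might see 3.1.1 and 3.1.3 as two rival primary models from which a result could be chosen after unblinding. Section 1.5 has the do-files prepared on blinded data and unblinding only after lock, and 1.2 blinds the analyst. The more natural reading is that 3.1.3 adds general rules to the model of 3.1.1. On that reading there is one model, but its covariate list is still open.
- **Gender and missing covariates.** A list given by example does not exclude gender. The SAP's silence on missing covariate values does not show that students would be dropped.
- **Sparse levels.** Only 3 boys' schools were selected, about one per arm, and each gender-stratified model has one empty level of nature of school. This is a fair constraint on the remedy. It does not justify omitting all three factors from the pooled model.

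**Conclusion.** The point holds in conditional form. The SAP allocates schools on three factors and includes none of them in any model. So far as they predict end-line BBSCQ beyond the school-level baseline score, standard errors will be too large and tests conservative. Assuming that they explain 10% to 50% of the residual between-school variance, widening is about 3% to 22% at the planned cluster size (about 3% to 15% if baseline explains half the between-school variance). It reaches about 29% to 30% at the achieved size with no baseline effect. If they explain nothing, there is no loss. These figures rest on the SAP's ICC of 0.02 and on assumed values of R². There is no indication of bias or inflated type I error, and the planned power is not at risk.

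Separately, the primary covariate set is not closed, because 3.1.3 adds an illustrative list that 3.1 and 3.1.1 do not carry. Both matters are worth correcting because the correction is cheap.

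**What to change.** 1. In 3.1.1, add type of school, school-size category and nature of school as fixed effects, alongside arm, school-level baseline BBSCQ and the school random intercept.
2. Carry the same factors into the secondary models where levels are neither empty nor too sparse. In the gender-stratified models, drop the empty level of nature of school and collapse sparse levels by a stated rule.
3. State whether the 3.1.3 socio-demographic covariates belong to the primary model or to a named sensitivity model. Either is defensible. Replace the illustrative wording with a complete list.

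The cost is SAP and do-file text, including the rule for sparse levels, up to 5 school-level degrees of freedom out of 74 schools, and intervals about 1% wider if the factors turn out not to be prognostic.

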## 1.1 Principal research objectives to be addressed

Primary objectives

1. To assess the effectiveness of the SEHER intervention plus Tarang-Adolescence Education Programme (AEP) delivered by the Teacher as SEHER *Mitra* (TSM) compared to AEP alone in building school climate as measured with Beyond Blue School Climate Questionnaire (BBSCQ) at 8 months.

2. To assess the effectiveness of the SEHER intervention plus AEP delivered by the SEHER *Mitra* (SM) compared to AEP alone in building school climate as measured with BBSCQ at 8 months.

Secondary objectives

3. To assess the effectiveness of the SEHER intervention plus AEP delivered by the SM compared to SEHER intervention plus AEP delivered by the TSM in building school climate as measured with BBSCQ at 8 months.

Sensitivity analysis will be performed for objectives 1, 2 and, 3 with those participants who have completed BOTH the base and end-line assessment.

4. Objectives # 1, 2 and, 3 will be analysed stratified by gender.

5. To assess the effectiveness of the i) SEHER intervention plus AEP delivered by the TSM compared to AEP alone; ii) SEHER intervention plus AEP delivered by the SM compared to AEP alone, and iii) SEHER intervention plus AEP delivered by the SM compared to SEHER intervention plus AEP delivered by the TSM in:

1. Improving attitudes towards gender equity as measured with adapted version of Gender Equitable Men Survey
2. Increasing knowledge and attitudes towards reproductive and sexual health (RSH) as measured with adapted version of WHO’s Illustrative Questionnaire for Interview with Young People
3. Reducing depression as measured with Patient Health Questionnaire-9 (PHQ-9)
4. Reducing self-reported experience of bullying behaviour as measured with adapted version of Illinois Bullying Scale
5. Reducing self-reported violence (perpetration and victimisation) as measured with adapted version of Global School-based student Health Survey (GSHS)

6. Objective # 5 will be analysed stratified by gender.

7. To measure the costs and cost effectiveness of the TSM and SM interventions in improving the school climate scores compared to the AEP alone.

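### Boys' and girls' effects come from separate models, with no arm-by-gender estimate and no rule for comparing them, so a split in significance may be misread as effect modification

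*SAP*

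**What the plan says.** Section 1.1 sets the objectives: "Objectives # 1, 2 and, 3 will be analysed stratified by gender" for the primary outcome, and "Objective # 5 will be analysed stratified by gender" for the secondary outcomes. Both cover three arm contrasts.

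Section 3.1.1 describes the gender analysis as an "Independent ANCOVA-type analysis for sample of only boys and girls, using a linear mixed effects model". Each fit has arm as a covariate and a school random effect, "adjusting for the school-level BBSCQ score at baseline". Section 3.1.2 applies a similar analysis to the secondary outcomes.

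Section 3.1.3 lists further covariates: "Socio-demographic variables such as age, marital status, caste, and parents’ education and occupation will be included as covariates". Gender is not named there, and no interaction is named anywhere. The interpretation rule, under the heading on multiple outcomes, is "Interpretation of the intervention effect will be based on the strength of evidence of effect size and consistency of results for related outcomes". It does not deal with boys against girls.

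The sample size text in section 1.2 claims "98% power to detect an effect size of 0.2 (difference in means/SD) school climate score" overall, and 88% among boys and 93% among girls for the same effect at an ICC of 0.02.

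**The concern.** The report will set boys' and girls' results side by side for three contrasts on one primary and five secondary outcomes: 3 × 6 = 18 pairs at least. Readers will compare them, and the plan gives them no valid way to do so. A difference in significance is not evidence that the effects differ. Two separate fits also do not supply the covariance needed to form a standard error for the difference, although 63 of the 75 selected schools are co-educational and so contribute pupils to both fits.

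At stake is the reading of two stated secondary objectives. The overall analysis of the primary outcome is not affected.

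**Working it through.** **Inputs (SAP section 1.2).** 24 schools (TSM) against 25 (comparison); 115 pupils per school (60 boys, 55 girls); 15% loss; ICC 0.02; effect 0.2 SD; two-sided 5%, read from 95% confidence. After loss, m = 97.75 overall, 51 boys and 46.75 girls per school.

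**Formula, in SD units.** SE = √{[1 + (m − 1)·ICC]/m × (1/k₁ + 1/k₂)}, with 1/24 + 1/25 = 0.08167. Power = Φ(effect/SE − 1.96).

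**The plan's own figures.**

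| Sample | SE | Power at 0.2 SD | Stated |
|---|---|---|---|
| All | √(2.935/97.75 × 0.08167) = 0.0495 | 98.1% | 98% |
| Girls | √(1.915/46.75 × 0.08167) = 0.0578 | 93.3% | 93% |
| Boys | √(2.000/51 × 0.08167) = 0.0566 | 94.2% | 88% |

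The overall and girls' figures reproduce. The boys' figure does not; it needs an ICC of about 0.03. The computed powers are therefore used below.

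**Chance of a split when the true effect is equal.** Let ρ be the correlation between boys' and girls' school effects. The SAP does not give it, so it is varied from 0 to 1. The covariance of the two estimates is ρ × 0.02 × 0.08167, so their correlation is 0, 0.25 and 0.50 at ρ = 0, 0.5 and 1. At ρ = 0 and 0.2 SD, the chance that exactly one fit is significant is 0.942 × 0.067 + 0.933 × 0.058 = 0.117. The other entries come from the bivariate normal distribution.

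| True effect in both | Power, boys / girls | ρ = 0 | ρ = 0.5 | ρ = 1 |
|---|---|---|---|---|
| 0.20 SD | 94% / 93% | 11.7% | 10.7% | 9.2% |
| 0.15 SD | 76% / 74% | 37.9% | 32.5% | 26.3% |
| 0.10 SD | 42% / 41% | 48.6% | 40.9% | 32.6% |

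**What a direct comparison would offer.** SE of the boy-girl difference = √(0.0566² + 0.0578² − 2·cov).

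| | ρ = 0 | ρ = 0.5 | ρ = 1 |
|---|---|---|---|
| SE (SD units) | 0.081 | 0.070 | 0.057 |
| Power, difference 0.2 SD | 70% | 81% | 94% |
| Power, difference 0.1 SD | 23% | 30% | 42% |
| Difference with 80% power | 0.23 SD | 0.20 SD | 0.16 SD |

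**Simplifications.** Every school is treated as having both genders, although 12 of the 75 are single-sex, and no gain from baseline adjustment is counted.

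**Sensitivity to cluster size.** The flow chart in section 2.1 shows larger end-line samples than planned, for example 4475/24 = 186 per TSM school. With 186 per school split 60:55 (an assumption, as end-line numbers by gender are not given), the chance of a split falls to about 3-4% at 0.2 SD but remains about 27-50% at 0.1 SD.

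**The case against.** The strongest reply is that the SAP promises stratified estimates and nothing more. They are pre-specified, carry their own power statements, and answer the question of how large the effect is in each gender. No claim of effect modification is planned, and section 3.1.3 sets no significant/non-significant rule. All of this stands: the problem is a risk of misreading that the plan leaves open, not an error it commits.

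A reader might infer four stronger things, which the document does not support:

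- **That the gender models adjust for a mixed-sex baseline score, which weakens them.** The SAP does not say which pupils form the score. Which version would adjust better depends on ρ, since an all-pupil mean averages more pupils. In a randomised comparison this affects precision and does not create apparent effect modification.
- **That shared schools make comparison by eye too ready to find a difference.** Positive correlation shrinks the standard error of the difference (0.081 at ρ = 0, 0.057 at ρ = 1), so treating the fits as independent is conservative.
- **That the split at 0.2 SD is 17%.** This follows from the stated powers under independence (0.88 × 0.07 + 0.12 × 0.93 = 0.173), but the 88% does not follow from the stated inputs.
- **That a joint model would resolve the single-sex schools.** It would not: those 12 schools inform only one gender's effect in any model.

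**Conclusion.** The point holds in limited form. Objectives 4 and 6 are served by separate fits, with no estimate of the difference between genders and no rule for stating one. With equal true effects and the planning inputs, a split in significance on the primary outcome has a chance of about 9-12% per contrast at 0.2 SD and 33-49% at 0.1 SD. This rests on an ICC of 0.02 in each gender and an assumed ρ between 0 and 1. At the larger end-line samples the risk at 0.2 SD is smaller, while at 0.1 SD it stays substantial. The figures are for the primary outcome; the secondary outcomes were not computed. The plan should be changed, but this concerns secondary objectives and their reporting.

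**What to change.** Keep the stratified estimates as planned. For each outcome, add one joint mixed model of all end-line pupils with arm, gender and arm-by-gender terms, the school-level baseline score, and a school random effect that lets boys' and girls' school effects differ (a random intercept plus a random gender slope). For binary outcomes, use the logistic form already chosen in section 3.1.2. Report the interaction for each contrast with its 95% confidence interval, and state that any claim of a gender difference will rest on that term only. In section 3.1.1, say whether the school-level baseline score in the gender models is formed from all pupils or from the gender analysed.

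The cost is one extra model per outcome and a few sentences of SAP text; no new data are needed. At planning sizes the interaction has less power than the main effect: about 70-94% for a 0.2 SD boy-girl difference and 23-42% for 0.1 SD. The SAP should say so, so that a non-significant interaction is not taken as proof of equal effects.
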